### Sample Size

The sample size for this study is determined based on the methodology outlined by Roy et al [8], which assessed the reduction in motor evoked potential (MEP) amplitude following intervention. Using an α level of 0.05 and a power of 90%, these parameters are incorporated into the 2-tailed formula for sample size calculation.

For a 2-sample comparison of means, the null hypothesis (H0: m1=m2) will tested, where m1 and m2 represent the means of 2 distinct populations. The assumptions for the calculation are as follows:

α=.05 (2-sided), Power=0.90, m1=12.85, m2=13.53, SD1=0.3, SD2=0.3, n2/n1=1.00

Based on these assumptions, the estimated required sample size is calculated to be 6 subjects per group. To account for potential dropouts, a 20% adjustment is applied, resulting in a revised sample size of 8 participants per group. Consequently, the total minimum sample size required for the study is 40 participants.

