### Experimental Groups

A total of 40 patients will be randomized into 5 groups using computer-generated random numbers. Patients will be categorized into placebo, rTMS, and iTBS to evaluate the efficacy of iTBS versus traditional rTMS on the primary motor cortex (MC). To determine the optimal site for iTBS application, stimulation was given at either MC or SC or combined MC+SC.

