#### Statistical Analysis

Data will be analyzed using STATA 14.0 software (StataCorp). Continuous variables will be presented as mean and SD, and categorical variables as frequencies and percentages. The primary analysis will be the intention-to-treat analysis, where baseline values will be carried forward for subjects with missing data. Unless stated otherwise, intention-to-treat data will be presented throughout the study. In addition, a per-protocol analysis will be conducted, including only participants who comply with the protocol.

Normality will be evaluated using the Shapiro-Wilk test for each outcome, homogeneity of variance will be checked using the Levene test, and the Mauchly test will be used for sphericity. Depending on the data distribution, parametric or nonparametric tests will be applied.

If the data are found to be uniformly distributed, we will use repeated measures ANOVA to assess changes over time within and between groups. Bonferroni or Tukey correction will be done for post hoc pairwise comparisons. Nonparametric tests like the Friedman test followed by appropriate post hoc tests will be used for skewed data. Corrections for multiple comparisons will be applied as specified to reduce the risk of type I errors. To analyze categorical variables, the chi-square or Fisher exact test will be used to assess associations between groups.

A *P* value less than .05 with a 95% CI will be considered statistically significant.

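### The 90% power is for one unadjusted two-group test, but pairwise comparisons among the five arms are to be corrected; at 6 evaluable per group, five-arm correction gives about 79–83%

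*Protocol article*

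**What the plan says.** **Sample Size.** The calculation is for a single test: "For a 2-sample comparison of means, the null hypothesis (H0: m1=m2) will tested". Its inputs are "α=.05 (2-sided), Power=0.90, m1=12.85, m2=13.53, SD1=0.3, SD2=0.3, n2/n1=1.00". From these, "the estimated required sample size is calculated to be 6 subjects per group". A 20% dropout allowance raises this to 8 per group, or 40 in all. The section mentions neither five arms nor any adjustment of alpha.

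**Experimental Groups, Mode of Stimulation, Site of Stimulation.** Patients are randomized to five groups, which serve two overlapping three-arm questions. Mode compares placebo, high-frequency rTMS and iTBS (groups 1–3). Site compares iTBS on the motor cortex, on the spinal cord and on both (groups 3–5). Group 3 belongs to both questions.

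**Statistical Analysis.** For suitably distributed data the plan is a repeated measures ANOVA within and between groups, and "Bonferroni or Tukey correction will be done for post hoc pairwise comparisons". The number of pairs is not given. The primary analysis is by intention to treat, with the baseline value carried forward where data are missing.

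**The concern.** The test that was powered is not the test that will be read. Sizing assumes that one pair of groups is compared at .05. The analysis compares pairs among five groups at a stricter level. Five groups form 5 × 4 / 2 = 10 pairs, so Bonferroni over all of them tests each at .05/10 = .005, and Tukey over five arms sets a similarly higher bar.

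If the correction spans all five arms, the stated 90% does not describe any comparison the trial will report, even with an assumed effect above two standard deviations. A negative pairwise result would then be read against a power figure that did not apply to it.

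**Working it through.** **Inputs** (Sample Size section): difference 13.53 − 12.85 = 0.68; SD 0.3 in both groups; two-sided alpha .05; power 0.90; 1:1 allocation; 6 evaluable and 8 enrolled per group. There are five arms (Experimental Groups). Standardized effect d = 0.68/0.3 = 2.267.

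**Formula.** For n per group, the t statistic for one pair is noncentral t with noncentrality d·√(n/2). Power is the probability that it exceeds the critical value in absolute size. At n = 6 the noncentrality is 2.267 × √3 = 3.926.

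**1. The plan's own figure.** One unadjusted two-sample t test (df 2n − 2) has power 87.9% at n = 5 and 94.2% at n = 6. So 6 is the smallest n that reaches 90%, and the stated figure reproduces. With dropout, 6/(1 − 0.2) = 7.5, rounded up to 8, and 8 × 5 = 40. Nothing is wrong with this arithmetic.

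**2. With correction, 6 evaluable per group.** The error is pooled over five arms (df = 5 × 5 = 25) except where noted. The Tukey critical value is the studentized range quantile divided by √2.

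| Family | Correction | Power for one pair |
|---|---|---|
| All 10 pairs | Tukey, k = 5 (critical value 2.937) | 82.7% |
| All 10 pairs | Bonferroni, .05/10 | 79.0% |
| 6 pairs (3 mode + 3 site) | Bonferroni, .05/6 | 84.4% |
| 3 pairs, each question its own family | Bonferroni, .05/3 | 90.4% |
| 3 pairs, each question its own family | Tukey, k = 3 | 91.6% |
| 3 pairs, error from those three arms only (df 15) | Bonferroni / Tukey | 87.4% / 89.2% |

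**3. How many are needed over ten pairs.** With pooled error, n = 7 gives 87.5% (Bonferroni) or 89.9% (Tukey), and n = 8 gives 92.9% or 94.4%. So ten-pair correction needs 8 evaluable per group. That is everyone enrolled, with none of the 20% dropout the plan allows for.

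**4. The intention-to-treat set.** The carry-forward rule keeps all 8 per group in the analysis, but dropouts enter as no change. I simulated 8 per group in five arms, assuming that the 0.68 and 0.3 apply to change scores, that one arm has the effect and the other four have zero mean change, and that each dropout contributes exactly zero. Ten-pair correction, pooled error (df 35):

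| Imputed per arm | Tukey | Bonferroni |
|---|---|---|
| 0 of 8 | 94% | 93% |
| 1 of 8 | 88% | 85% |
| 2 of 8 | 76% | 71% |

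The plan's 20% dropout is 1.6 of 8, between the last two rows.

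**The case against.** The strongest reply is that correction over all ten pairs is an inference. The Statistical Analysis section never says all pairs or ten, and the group descriptions naturally split into two three-arm questions. If each is its own family, power at 6 per group is about 87–92%, so the stated 90% is roughly kept. This stands, and it is why the point cannot be put as a flat failure of the 90%. However, the article does not state that reading. Tukey over the five-arm ANOVA would be an all-pairs procedure, and two separate families would leave error across the two questions uncontrolled although they share group 3.

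Second, six completers is not the primary analysis set, because carry-forward keeps all 8. That is correct, and with 8 complete the ten-pair power is 93–94%. With imputed dropouts it falls below 90% under the assumptions shown.

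Three stronger readings are tempting and are not supported:
- A reader might compute 64% (63.6%) for Bonferroni over ten pairs. That uses a separate two-sample error with 10 degrees of freedom for each pair. The planned comparisons follow an ANOVA, where the pooled error is usual.
- A reader might infer from the wording "Bonferroni or Tukey correction will be done for post hoc pairwise comparisons" that the choice between the two methods will wait until the data are seen. The article does not say so, and an analysis plan that is not shown may settle it.
- A reader might infer that the sample size arithmetic is wrong. The 6, the 8 and the 40 all reproduce.

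**Conclusion.** The point holds in a limited form. The sample size allows for no multiplicity, the analysis corrects for it, and the family of comparisons that links the two is not stated. At 6 evaluable per group, power for one pair is 79–83% if the correction spans all ten pairs and 84% with Bonferroni over the six mode and site pairs. That is 6 to 11 points below the 90% stated. It is close to 90% only with two separate families of three, and it exceeds 90% over ten pairs only if all 8 per group contribute complete data.

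The figures rest on the protocol's own effect and SD, normal data with equal variances, pooled ANOVA error and a between-group comparison at one time point. The within-patient correlation needed for a full repeated-measures calculation is not given. The 90% itself concerns MEP amplitude, whereas the primary outcome is the ASIA score; that is a separate matter which this point does not address. Confidence is medium, because the size of the shortfall depends on a family that the article leaves open.

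**What to change.** In the Statistical Analysis section, state the family of confirmatory comparisons that follows from the mode and site questions. It could be one primary contrast tested at .05, or a short list fixed in advance, with all other pairs labelled exploratory. Name one correction procedure and say that it uses the pooled ANOVA error. In the Sample Size section, restate the power at that adjusted level for the existing 40 patients, and say how carried-forward dropouts enter the figure.

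The investigators should choose the list. As one example, motor cortex iTBS could be compared with placebo, rTMS, spinal cord iTBS and combined iTBS. Bonferroni over these four gives 88.1% at 6 per group with pooled error. A fixed sequence gives 96.5%, but only for its first contrast. This list also leaves out rTMS versus placebo and spinal cord versus combined stimulation, both of which bear on the protocol's own questions.

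The change is wording only and needs no added patients. The cost is that the restated power may fall below 90%, and comparisons outside the family will carry no confirmatory P value.

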### Inclusion and Exclusion Criteria

Adults aged 18 to 60 years with a thoracolumbar (T1-L5) SCI and complete motor loss below the lesion level (American Spinal Injury Association [ASIA] score A) will be screened and recruited within 1 month of injury.

Exclusion criteria include patients with osteoporotic fractures, a history of neurological or orthopedic diseases affecting the SC, head injuries, ferromagnetic metallic implants near the target stimulation area, pacemakers, cognitive impairment, pregnancy, a history of seizures, or acute eczema or bedsores.

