### Patient Recruitment and Parameter Recording

Participants will be enrolled from the Jai Prakash Narayan Apex Trauma Centre at AIIMS (All India Institute Of Medical Sciences) Delhi. Following SCI surgery, a 15-day period will be designated for vertebral stabilization, after which sutures will be removed on the 15th day. Once the sutures are removed, baseline parameters will be measured. Patients will then be randomly assigned to one of the intervention groups. After completing the intervention, postintervention parameters will be recorded and follow-up assessments will be conducted at 1, 2, and 3 months (Figure 2). To ensure consistency during the intervention, all assessments will be recorded by the blinded primary investigator.

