### Outcomes

#### Primary Outcome (Neurological)

The primary outcome will measure the severity of injury with the ASIA Scoring System. The ASIA impairment score (AIS) ranges from complete loss of sensation and movement (AIS=A) to normal neurological function (AIS=E). The ASIA motor score uses a test of the strength of 10 key muscles on each side of the body (eg, elbow flexors, wrist extensors, hip flexors, quadriceps, and dorsi flexors). The score ranges from 0 (no contraction) to 5 (normal resistance) through a full range of motion. A total possible score of 50 for the upper extremities and 50 for the lower extremities may be obtained [11]. The ASIA sensory score involves pinprick and light touch sensation at key points representing each dermatome of the body, scored on a 3-point scale (0, 1, and 2). Scores are summed to give a total possible score of 224, where a higher score indicates better sensation than a lower score.

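### The tests named for categorical variables ignore the order of the AIS grades, and no route named in the plan is clearly suited to comparing that ordered grade between arms

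*Protocol article*

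**What the plan says.** Under Primary Outcome (Neurological), the protocol article states: "The primary outcome will measure the severity of injury with the ASIA Scoring System". Three measures are described there: the AIS grade, running from A to E in order of recovery; a motor score; and a sensory score. Under Inclusion and Exclusion Criteria every patient enters at grade A. Under Patient Recruitment and Parameter Recording, "postintervention parameters will be recorded and follow-up assessments will be conducted at 1, 2, and 3 months", so each patient has four post-baseline grades.

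The Statistical Analysis section names three routes:
- repeated measures ANOVA, with Bonferroni or Tukey post hoc comparisons, for data that pass the distribution checks;
- for the rest, "Nonparametric tests like the Friedman test followed by appropriate post hoc tests will be used for skewed data";
- for categorical data, "To analyze categorical variables, the chi-square or Fisher exact test will be used to assess associations between groups".

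No sentence assigns the AIS grade to any of them. The Sample Size section rests on motor evoked potential means and gives 8 patients in each of 5 groups. It states no power for AIS.

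**The concern.** Everyone starts at A, so any treatment effect on AIS shows as how far patients move up the scale. That movement is ordered. Chi-square and Fisher give the same answer if the grade labels are shuffled, so they cannot tell an arm whose patients reach D from one whose patients reach B, except as different labels. They spread the evidence over every possible difference in pattern.

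Friedman does use order, but it asks whether grades change across visits within patients. It does not compare arms, which is the randomised question. Repeated measures ANOVA does compare arms, but it is reserved for data with a suitable distribution, and a five-level grade that starts at A for everyone is a poor candidate.

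At stake is a real upward shift in AIS being reported as no association, in a trial whose Limitations section already concedes that a small sample may reduce power.

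**Working it through.** **Plan's own sample size.** Inputs from Sample Size: "α=.05 (2-sided), Power=0.90, m1=12.85, m2=13.53, SD1=0.3, SD2=0.3, n2/n1=1.00". The normal approximation is n = 2(1.960 + 1.282)² × 0.3² / (13.53 − 12.85)² = 2 × 10.51 × 0.09 / 0.4624 = 4.09, so 5. The two-sample t solution is 5.27, so 6. Then 6 / 0.8 = 7.5, so 8, and 5 × 8 = 40. The plan's figures reproduce. They concern motor evoked potentials and carry no information about AIS.

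**Why order matters.** For 5 arms and 4 occupied grades, chi-square has (5 − 1)(4 − 1) = 12 degrees of freedom and Kruskal-Wallis has 5 − 1 = 4. Expected counts are also tiny. If 80, 10, 7 and 3% of patients fall in grades A to D, 8 per arm gives 6.4, 0.8, 0.56 and 0.24. P values should therefore be exact or by permutation, as in the five-arm check below.

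**When order cannot matter.** If patients only stay at A or move to B, there are two columns. The tie-corrected Kruskal-Wallis statistic then equals (N − 1)/N = 39/40 times the chi-square statistic, so the permutation P values are identical and the gain is exactly 0. The two-arm calculation agrees: for 10% v 50% moving to B with 8 v 8, Fisher and exact Wilcoxon both have 22% power.

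**Simulation, one visit, five arms of 8, two-sided 0.05.** The documents supply the arms, the 8 per arm and the alpha. The rest is assumed: 50, 80 or 95% of control patients at A, the others spread over higher grades; a proportional odds ratio (OR) of 5 or 15; and the effect either equal in four arms or rising in equal steps on the log-odds scale. Each row shows two runs of 300 trials. They differ only in within-patient correlation, which plays no part at a single visit, so the spread between them is simulation error.

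| Control at A | Effect pattern | OR | Chi-square, % | Kruskal-Wallis, % | Gain, points |
|---|---|---|---|---|---|
| 95% | rising | 5 | 5.3; 5.7 | 8.0; 5.3 | 2.7; −0.3 |
| 95% | four equal | 15 | 15.3; 17.3 | 25.3; 26.7 | 10.0; 9.3 |
| 80% | four equal | 5 | 11.3; 18.0 | 20.7; 25.3 | 9.3; 7.3 |
| 80% | rising | 15 | 39.7; 38.3 | 61.3; 64.3 | 21.7; 26.0 |
| 50% | four equal | 5 | 17.3; 19.7 | 29.0; 37.0 | 11.7; 17.3 |
| 50% | rising | 15 | 39.3; 40.7 | 73.3; 73.3 | 34.0; 32.7 |

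With no effect, the rejection rates were 3.3% and 3.2%, so the gain is not bought with false positives. The Monte Carlo standard error of a single figure is at most √(0.25/300) = 2.9 points.

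**Second set of assumptions.** With a normal latent score shifted by d standard deviations (800 trials per setting), Kruskal-Wallis at the last visit gained about 1 to 4 points at d = 0.5, 8 to 14 at d = 1 and 18 to 27 at d = 1.5 to 2.

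**Pairwise, 8 v 8, Fisher v exact Wilcoxon.** Control 95% at A, OR 5: 1% v 1%. Control 80% at A, OR 10: 40% v 49%. Control 50% at A, OR 10: 43% v 65%. After Bonferroni over 5 × 4 / 2 = 10 pairs (0.05/10 = 0.005), the last two become 11% v 14% and 13% v 23%.

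**The case against.** The strongest reply is that the plan never sends AIS to chi-square or Fisher. Its nonparametric list is introduced as examples, so a suitable ordinal test could be among those intended, and a condensed article may leave the assignment to a fuller document. The motor and sensory scores, which belong to the same primary outcome, have their own route. A chi-square or Fisher test at one visit is also valid; it is only inefficient. All of this stands. It limits the point to a conditional one, but does not remove it: the only test stated for categorical data ignores order, and the only nonparametric test stated does not compare arms.

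Three stronger readings are tempting, and the documents support none of them.
- A reader might infer a fixed, substantial loss of power. No AIS distribution or effect size is given, and the loss can be nil.
- A reader might infer that the four visits per patient would be stacked in one table, which would invalidate the P values. Nothing in the plan proposes this.
- A reader might infer that a test using all visits must do better still. That depends on the time course, which the documents do not give. If the effect builds up to 3 months, a rank test on each patient's mean grade can have less power than chi-square at the last visit: 31% v 36% at d = 1.5 and correlation 0.9, and 49% v 68% at d = 2.

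**Conclusion.** The concern holds in a limited form. As written, the plan leaves the AIS grade without a clearly suitable between-arm test, and the one stated for categorical data discards the order of the grades. If that test is used at one visit, the cost runs from about 0 points of power to about 20 to 34 points. The low end applies to small effects, nearly all patients staying at A, or moves only from A to B; the high end to large effects spread over several grades. This range rests on assumed grade distributions and effects, and on proportional odds or a normal latent shift. Where the plan's AIS analysis falls within it cannot be told from the documents.

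The change improves efficiency and does not rescue the comparison. With moderate effects the ordinal test still has low power at 8 per arm, and corrected pairwise tests have less.

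**What to change.** Add one sentence to Statistical Analysis: the AIS grade will be compared between arms at one prespecified visit, for example 3 months, by a Kruskal-Wallis test, followed by pairwise Wilcoxon rank-sum tests with a stated multiplicity correction, all with exact or permutation P values. Restrict chi-square and Fisher to unordered variables. AIS frequencies by arm can still be tabulated at every visit.

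The cost is a line of text, with no added patients, visits or data. The one small downside is that a rank test responds to an overall shift and is less sensitive to a non-monotone pattern, such as one arm having both more A and more D than another.

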#### Ethical Considerations

Ethical approval has been obtained from the Institutional Ethical Committee of All India Institute of Medical Sciences, Delhi (Project Ref. Id: IECPG/551/7/2022). The study is registered in the Clinical Trials Registry- India (CTRI; reference number CTRI/2022/11/047038). Informed, voluntary, and written consent will be taken, and the participants will be given a choice to withdraw from the study at any given point in time. They will be duly informed of the duration of the study along with any potential risks or side effects associated with TMS intervention. If a patient experiences an adverse event during the trial, the investigators will provide treatment and corresponding financial compensation. No names or any other forms of identification will be used in publications or reports resulting from the study without the permission of the participants.

All the experiments will be carried out in the Brain Stimulation and Neuromodulation Laboratory, Department of Physiology, and CARE, Department of Psychiatry, AIIMS, New Delhi.

## Results

This randomized controlled trial will assess the impact of iTBS on motor and sensory functional recovery, alterations in corticospinal excitability, biomarkers, and quality of life in patients with cSCI. The project was funded by DBT in July 2019. The randomized controlled trial has been registered with the Clinical Trials Registry-India (CTRI/2022/11/047038) and ethical approval obtained from the Institutional Ethics Committee, AIIMS, Delhi (Project Ref. Id: IECPG/551/7/2022). The project was initiated in January 2023 and is likely to be completed by June 2025. The results of this study will be analyzed from January to July 2025 and will be submitted for publication in peer-reviewed scientific journals. We presume this study may support integrating iTBS into a rehabilitation program for motor and sensory recovery in patients with cSCI.

## Discussion

### Principal Findings

SCI significantly impairs the corticospinal integrity and afferent-efferent input-output circuitry. Theoretically, the pyramidal tract is the primary neural pathway that links the cortex and SC to facilitate the movement of distal extremities. The primary purpose of any treatment is to reconstruct the neural circuit immediately after SCI for functional sensory-motor recovery. To facilitate neural circuit reconstruction, it is required to stimulate nerve cell sprouting and regeneration as well as increase the strength of the existing neuronal connections. Previous research demonstrated that individuals with incomplete SCI can benefit from locomotor training to enhance their motor skills. Rehabilitation programs may use learning and relearning mechanisms, uncovering a previously inactive synapse, and forming a new synapse [24]. However, the reconstruction of the damaged neural circuit is quite difficult with locomotor training alone. Studies have shown that the functional effects of exercise along with transcranial magnetic stimulation, can activate spared neural pathways and enhance the possibility of neural reconstruction [25,26].

TMS induces electrical currents in underlying cortical areas, depolarizes neurons, and generates an action potential that modulates the activity of spinal motor neurons and target muscles via the corticospinal tract. Repetitive transcranial magnetic stimulation as well as iTBS is an intervention in various psychiatric and pain conditions. In SCI, few studies suggest improvement in locomotor function, spasticity, and pain in incomplete patients [6]. Although, the functional mechanism of rTMS or iTBS on sensorimotor recovery in patients with SCI is not fully understood, but thought to induce synaptic plasticity via LTP or LTD-like effects [27], thereby promoting functional recovery in patients with SCI.

In addition, SC stimulation can modulate the activity of the local central pattern motor generators, which promotes synaptic strengthening [28]. In rat models of complete and incomplete SCI, a significant attenuation of glial scaring, lesion volume, neurotransmitter imbalance, muscle atrophy, and facilitation of neuronal survival, axonal regeneration, and myogenesis has been shown following whole-body magnetic field exposure [29,30]. Therefore, we propose that SC stimulation along with motor cortical stimulation would attenuate secondary damage and promote regeneration even in patients with cSCI, leading to long-term functional recovery.

Various single- and paired-pulse paradigms of TMS have been used for the assessment of cortical excitability, plasticity, integrity of the corticospinal tract, and excitatory-inhibitory neural circuitry of the motor cortex. We shall use all paired-pulse paradigms (short-interval intracortical inhibition, intracortical facilitation, and long-interval intracortical inhibition) to objectively assess excitatory-inhibitory neural circuitry and single-pulse paradigms (RMT, MEP, recruitment curves, and contralateral silent period) for unraveling the excitability of corticospinal circuitry and motor units.

